#### End-of treatment Questionnaire

Clinicians are asked, at the completion of each individual treatment, questions regarding whether there were any barriers to the family’s participation in treatment, support from other services, and dosage.

#### Implementation quality

Implementation quality at the organizational level is assessed by conducting interviews with clinic supervisors, team leaders and therapists in the participating clinics. The interview for clinic supervisors and team leaders consists of 27 items targeting uptake, satisfaction, challenges with and integration of MATCH in their clinics, and whether any organizational adjustments had to be made to comply with MATCH. Therapists are asked to respond to questions regarding satisfaction with training and ongoing consultation, leadership support, and organizational adjustments. Clinic supervisors and team leaders are interviewed three times during the study period, twice mid-study and once at the end of the study. Therapists are interviewed twice, once mid-study and once at the end of the study. The interview for both leaders and therapists is based on the Fixsen et al. [9] synthesis on implementation research.

#### Quality of treatment delivery and fidelity

All therapy sessions are videotaped. The focus of the recordings is the therapists’ delivery of treatment. Both MATCH and TAU therapists videotape their sessions. Data from these videotaped sessions will be used to assess the degree to which MATCH is delivered with competent adherence (for the MATCH therapists) and how well therapists in both conditions are able to involve the families, communicate with families, and establish a treatment environment conducive to therapeutic gains. All use of the videotaped material will entail coding of the films. Coding of videotapes are, however, contingent upon funding.

### Design and power

The trial is a randomized controlled effectiveness trial conducted in existing child and adolescent outpatient clinics in Norway. Participants are randomized within each site, following a computer-generated list with each participant having a 50% chance of being assigned to either group. The results of the randomization are provided to the clinic for each new case. The process is as follows:*Referral*: children and their families are referred to the participating clinics (primarily by either their general physician, head of the municipal child welfare agency, or community psychologist) for child symptoms of anxiety, depression, trauma-related problems and/or conduct problems. Children and families are assessed for eligibility for the study based on these referral reasons, and on whether they have significant symptom levels meeting study cut-offs at the time of screening (see item c and “Rationale for the use of cut-off scores” below)*Consent*: once found eligible at this stage, families are informed of the trial by the contact person at the clinic. If the family consents, their contact information is given to the Norwegian Center for Child Behavioral Development (NCCBD) which then registers the information and contacts the family to provide more information about the trial and to ask whether the family wants to participate. The family is informed briefly about the treatment options and that random assignment is involved. If the family agrees, a consent letter, along with a brief study description (including contact information of the study personnel), is sent to the family. The NCCBD then registers receipt of a signed consent from the family. A phone call is made to the family within a few days to make sure that they have received the letter in the mail. If the NCCBD has not received a signed consent within 2 weeks, another phone call is made to the family, to allow for questions and to urge interested families to sign and send in the consent form.*Pre-assessment and decisions about inclusion to the trial*: upon receipt of a signed consent form from the family, the pre-intervention assessment (wave 1) is sent out to the family This is done approximately 2 weeks prior to the date set for their first consultation at the clinic. A reminder is sent out to the family after 1 week, and is followed up by weekly phone calls if they have not submitted the completed assessment. The pre-intervention assessment, on which scores are based to assess eligibility to the trial, include the CBCL, YSR, KATE and if relevant (given the scores on the KATE), the child and parent version of CATS. Children between the ages of 8 and 11 years complete these questionnaires at the clinic together with a clinician. The family is eligible if the child’s scores are at or above clinical cut-off scores.*Further assessment by the clinics and setting the primary protocol*: the clinics receive the summary scores on the CBCL, YSR, KATE, and CATS from the NCCBD. In some cases, the clinics administer these questionnaires directly to the families as part of their routine, and in these cases, the NCCBD receives the results from the clinic(s), after collected consent. For children with T-scores above the cut-off, a therapist at the clinic conducts a TPA. Based on the result from these assessments, MATCH consultants make the decision about the child’s primary protocol to be tried first (primary problem area). MATCH consists of four treatment protocols, one for each problem area; anxiety, depression, trauma, and conduct problems*Randomization*: once inclusion to the study and primary protocol are determined, the family is randomized to either the MATCH condition or the TAU condition. Information about the outcome of the randomization procedure is then provided to the clinic. The outcome of the randomization then triggers two events: (1) the dates for the time-invariant assessment points (i.e., the 3-, 6-, and 15-month assessments) and (2) the clinics being alerted to inform the NCCBD of who the therapist for the family will be, along with their contact information*Registration in PATH*: families are then added to the PATH system a week prior to their first meeting with their appointed therapist. The families receive an email on the Sunday of each week asking the parent and the child (if they are over 8 years old) to fill out a questionnaire, consisting of the TPA and the BFS. The TPA and the BFS are collected weekly (or between each session) as part of the PATH system of user feedback

#### Rationale for the use of cut-off scores in assessing eligibility for study participants

Potential study participants are first assessed with the Achenbach System of Empirically Based Assessment (ASEBA:CBCL and YSR) and CATS. Participants who score at or above 1 standard deviation on at least one of the broadband scales (externalizing and internalizing, a T-score at or above 60) of either the CBCL or the YSR, are defined as meeting the inclusion criteria. Additionally, any patient scoring at or above 1.5 standard deviations on any of the relevant sub-scales of the CBCL or the YSR (e.g., aggressive behaviors or anxious-depressed) are accepted for study participation (a T-score at or above 65).

Moreover, all patients having a score at or above 15 on CATS are also deemed eligible for study participation. This cut-off is based on recommendations from the Norwegian translators and expert users of CATS (Norwegian Center for Violence and Traumatic Stress Studies, NKVTS). CATS is a revision of the Child PTSD Symptom Scale (CPSS), with some added items to cover the diagnostic criteria of DSM-V. A clinical cut-off for CPSS is a score of 11 or above [10], but because the CATS contains four additional items to be scored from 0 to 4, the cut-off for CATS is set to 15.

#### Primary outcomes

CBCL/YSRCATSWeekly PATH scores: TPA and BFS (throughout treatment)Time in therapy

#### Secondary outcomes

KIDSCREEN-10SCL-5Treatment satisfactionQuality of treatment delivery and fidelity

#### All additional measures administered during the trial

Demographics and background informationChild medicationTherapist allianceExperience with evidence-based practiceImplementation quality

### Procedures

#### Intervention/Route of administration

When the child and family have been randomized to a MATCH therapist, the therapist will also be informed regarding the child’s primary protocol. The therapist will bring the case to the consultation group led by a US consultant and receive consultation on how to start the treatment. The therapist will arrange with the family when to meet and the treatment will then be delivered at the clinic. The assigned primary protocol (either anxiety, trauma, depression, and/or conduct) will lead the sequence of modules used. A treatment will always involve more than one module. To manage clinical interference that requires deviation from the primary protocol, the therapist, in agreement with the consultant, can choose among several of the 35 modules. If there are any remaining difficulties that need to be addressed after the primary protocol has been completed, the therapist can start a new protocol.

Children and families in the comparison group, who receive TAU, are offered the treatment normally delivered in the clinic. The content and structure of TAU vary among clinics and among individual therapists. TAU therapists may deliver family-based therapy based on an eclectic approach; they may offer a standard, single-syndrome EBT (for example, Coping Cat or Parent Management Training) or enroll the child or family in group therapy. Families in both conditions complete PATH, but only MATCH therapists will have access to the families’ responses. Therapy sessions of both conditions are videotaped, with the exception of children and families in the TAU condition who take part in group-based therapy (due to data confidentiality restrictions on children and families who are not part of the study). See the trial Standard Protocol Items: Recommendations for Interventional Trials (SPIRIT) Checklist for details (in Additional file 1).

#### Interventions

MATCH-ADTC is the experimental condition, as described above. Children and families in the TAU condition will receive treatment as it is usually delivered in the clinic.

#### Treatment permitted and not permitted during the trial

Children and families in the MATCH condition will receive the MATCH treatment only. The sole exception is that the children may receive a medication regimen deemed necessary by the clinician. Medication use is registered and tracked throughout the treatment period for all participants. No restrictions are imposed on what is offered to the children and families in the TAU condition. There are also no restrictions for participants in either condition regarding prior treatment or prior participation in any EBTs.

#### Procedures for monitoring participant compliance

Children and parents answer the weekly PATH questionnaire, which assesses treatment progress. Questionnaires of the PATH system are sent out automatically every Sunday, and a follow-up email is sent every Tuesday. If families fail to fill out questions in the PATH system, they are reminded to do so by members of the research team. The research team at the NCCBD also remind children and families to fill out the questionnaires at the various data collection waves. This is done regularly by phone, text message, or email.

#### Dosage

The MATCH treatment is delivered in weekly or bi-weekly sessions. Each session lasts 45–60 min. Although parents are usually more involved when conduct problems are the primary treatment focus, parent involvement is also emphasized when the treatment targets anxiety, depression, or trauma. There are separate modules for psychoeducation for parents in all the treatment protocols. In addition, when children meet with their therapists alone, parents are invited to participate in the last 10–15 min of the sessions to make sure they get a proper understanding of the skill the child is about to learn, and of how to support the child in doing the homework assignment for the coming week. It is a pronounced goal that the parents eventually take over functions that the therapist has had, in terms of facilitating and motivating the child to use new skills and to continue practicing.

#### Treatment period

There is not a set number of sessions; the MATCH therapist follows the flowchart for the primary protocol. The therapist moves on to a new module when the content of the module in question has been properly covered or when the clinical concern addressed by the module has resolved. If there is interference that prohibits the therapist from following the prescribed sequence, the therapist can use modules from a different protocol until the interference is resolved. Treatment will end when the PATH data show reasonable progress, combined with the clinical judgment that most of the improvement that is likely to happen, has been achieved. As in all treatments, some cases will not have the expected progress, and the therapist will discuss with the consultant whether another approach would be appropriate. In an article reporting on the effects of MATCH in the US, the average number of therapy sessions was 30.02 and because most sessions are conducted weekly, the average time period for treatment was about 7.5 months [23]. There are no accurate statistics available indicating what the average time in therapy is for TAU in Norway. One of the goals of this study is, however, to compare time in treatment between the two conditions.

#### Description of stopping rules (discontinuation criteria)

##### Individuals

If the therapist (in agreement with the clinic supervisor) uncovers acute suicidality, psychosis, self-harm, abuse, or maltreatment in the family, any of the exclusion criteria, or other situations that render the MATCH treatment or regular practice not viable or safe. If the child is placed out of home and/or parents’ lose custody of the child. Withdrawn consent from the study or treatment.

##### Parts of the trial

If a site or a therapist does not follow through on trial requirements or agreements.

##### The entire trial

Withdrawn government funding (to the NCCBD), breach of ethical standards or regulations. If any of the participating mental health outpatient clinics uncovers any serious adverse events due to the treatment, leading them to conclude that it is not safe to offer MATCH to patients.

### Statistical analyses

We plan to conduct several analyses, each of which will answer different hypotheses and have its own type of statistical analysis.

#### For main effects

The time-variant assessments, that is, the pre-, post-, and follow-up assessments, will be analyzed using descriptive statistics and general linear models (GLM), controlling for age, gender, type of problem area, and family background information (e.g., SES).

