**Methods/design:**

Participants will include 280 children (aged 6–14.5 years at intake) who receive treatment in child and adolescent mental health outpatient clinics in Norway, and their families. Families are randomly assigned to either the experimental group receiving treatment from therapists trained in MATCH, or to the comparison group receiving treatment from therapists delivering treatment as usual (TAU). Data on children’s symptomology, child and family functioning, demographics, background information, and mental health outcomes are collected as well as frequent feedback on treatment response, plus video-recordings of treatment sessions and implementation quality scores from each participating clinic. Questionnaires are administered in six waves.

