#### Level of significance to be used

In most analyses, a significance level of α = .05 will be used for main effects analyses, mediation models, growth curve models, and general models of association. We will use more stringent alpha levels in subsequent analyses in cases where many variables are entered into prediction models, to reduce the risk of Type 1 error.

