### Sample size

#### The number of subjects planned to be enrolled

We plan to recruit 280 children and their families. Based on a power analysis for the analysis of main effect, we concluded that a sample size of 280 will detect an effect size of 0.3, provided power of .80, at an alpha level of .05.

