#### The number of participants projected at each site

The number of families to be recruited at each site was calculated based on the number of therapists trained at each site, with the expectation that each MATCH therapist would contribute with at least six cases each to the study, matched by an equal number of cases from TAU therapists. Six clinics participate at the present. Originally, one more outpatient clinic was recruited to take part in this trial. In the fall of 2016, however, it became clear that this clinic was not able to fulfill the requirements of participation and was, therefore, excluded from the trial, from therapist consultation, from the use of the PATH system, and all other MATCH elements. This decision was reached in agreement with the management at the clinic in question. We had originally planned to recruit 36 families from this site. Thus, the remaining six clinics have been asked to recruit, between them, the remaining families to compensate for the loss. As of fall 2017, we are in the process of recruiting two or three more clinics.

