### Quality assurance

Quality assurance of MATCH therapists is achieved by weekly online video meetings with the US consultants and the Norwegian co-consultants. During the consultation, which is based both on information from the PATH data and on a short summary of what happened in the last session provided by the therapist, the consultant asks specific queries to monitor whether the therapist adheres to the treatment principles of MATCH. The focus of the consultation is to plan treatment, based both on the families’ feedback in PATH and the therapists’ clinical judgments, in accordance with the flowchart for the primary protocol. Obstacles and problem-solving strategies are discussed, and the therapist and US consultant arrive at a plan for the next session. The consultant will often model new procedures in these Skype meetings. In addition, there is a weekly preparation meeting with the Norwegian co-consultant in which PATH entries are reviewed, and the therapists and their designated co-consultant role-play in Norwegian to prepare the delivery of new modules and to ensure adherence to the model. The consultation by US consultants is led in English and the pre-consultation call is led in Norwegian by the Norwegian consultants. The consultation also addresses basic principles and theoretical understanding behind the interventions, and individual tailoring of the treatment, including age-appropriate adaptation.

The format of the consultation is in-group case supervision guidance. Consultation groups consist of two to four therapists, together with a US consultant and a Norwegian co-consultant. Case-relevant modules are reviewed and often modeled by the US consultant. The consultation also addresses basic principles and theoretical understanding behind the interventions, and individual tailoring of the treatment, including age-appropriate adaptation.

The Norwegian co-consultant sets up role-plays for the therapists in the following prep call, in order for the therapists to train in new skills, and for the co-consultant to give feedback regarding performance.

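### The main-effects general linear model has no therapist term although therapists are nested in arm, so its standard error is too small for any positive therapist ICC

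*Protocol article*

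**What the plan says.** Under For main effects, the time-variant assessments "will be analyzed using descriptive statistics and general linear models (GLM), controlling for age, gender, type of problem area, and family background information". Neither therapist nor site is named. Under Level of significance to be used, "a significance level of α = .05 will be used for main effects analyses".

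Mixed-effects regression and growth curves appear in the next analysis section, For effects according to time-invariant assessments. They are meant for trajectories over the pre, 3-, 6- and 15-month data and the weekly PATH data, and no therapist level is mentioned there either.

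The design is described in four other places:

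- Abstract, Methods/design: families go to the "experimental group receiving treatment from therapists trained in MATCH, or to the comparison group receiving treatment from therapists delivering treatment as usual (TAU").
- Design and power: "Participants are randomized within each site, following a computer-generated list with each participant having a 50% chance of being assigned to either group". The randomisation result also prompts the clinic to report which therapist the family will have.
- The number of participants projected at each site: the expectation is that "each MATCH therapist would contribute with at least six cases each to the study, matched by an equal number of cases from TAU therapists".
- Quality assurance: "Consultation groups consist of two to four therapists, together with a US consultant and a Norwegian co-consultant".

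The power statement, under The number of subjects planned to be enrolled, is that "a sample size of 280 will detect an effect size of 0.3, provided power of .80, at an alpha level of .05". It mentions no design effect.

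**The concern.** Randomisation is by family, but treatment comes through a therapist who belongs to one arm only. Differences between therapists therefore do not cancel in the MATCH-minus-TAU contrast; they add to its variance. A general linear model in its ordinary sense assumes independent residuals, and covariates such as age, gender, problem area and family background do not absorb therapist differences.

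Some between-therapist variation is plausible on the article's own account: the section on Intervention/Route of administration says that TAU differs from clinic to clinic and from therapist to therapist. Shared consultation groups are a further possible source of correlation in the MATCH arm; they are not counted in the figures below.

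The post-treatment and follow-up comparisons on CBCL, YSR and CATS answer two of the three questions under the first aim. An understated standard error there makes confidence intervals too narrow and a false claim of a difference more likely. A model without therapist variance also speaks only for the therapists who took part, whereas the aim concerns children treated in Norwegian outpatient clinics.

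**Working it through.** **Inputs from the article.** N = 280, so 140 per arm at 1:1; effect size d = 0.3; power 0.80; alpha 0.05, sidedness not stated; at least six cases per MATCH therapist.

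**Assumptions.** Therapist ICC from 0.01 to 0.10. Cluster size m = 6 in MATCH. In TAU, either m = 6 as well (both arms clustered) or one case per therapist (only MATCH clustered). With six cases each, 140 / 6 is about 23 therapists per arm.

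**The plan's own figure.** With independent children, n per arm = 2(z_alpha + z_power)² / d².

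- One-sided: 2(1.645 + 0.842)² / 0.09 gives 138 per arm, 276 in total; power at 140 per arm is 0.81. This reproduces 280.
- Two-sided: 2(1.960 + 0.842)² / 0.09 gives 175 per arm, 350 in total; power at 140 per arm is 0.71. It matches 280 only if covariates explain 20% of the variance (350 × 0.80 = 280), which the article does not state.

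Both routes assume independent children.

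**Effect of clustering on the stated test.** The design effect is DE = 1 + (m − 1) × ICC. The variance factor V equals DE if both arms are clustered, and (DE + 1) / 2 if only MATCH is. The true standard error divided by the reported one is √V, and the actual two-sided error rate is 2(1 − Φ(1.96 / √V)).

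| ICC (assumed) | V, both | SE ratio | Actual rate, both | V, MATCH only | Actual rate, MATCH only |
|---|---|---|---|---|---|
| 0.01 | 1.05 | 1.02 | 5.6% | 1.025 | 5.3% |
| 0.02 | 1.10 | 1.05 | 6.2% | 1.05 | 5.6% |
| 0.05 | 1.25 | 1.12 | 8.0% | 1.125 | 6.5% |
| 0.10 | 1.50 | 1.22 | 11.0% | 1.25 | 8.0% |

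Since the article says at least six, larger loads are possible: with m = 10 in both arms and ICC 0.05, DE = 1 + 9 × 0.05 = 1.45 and the rate is 10.4%.

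**Simulation check.** Null trials with 23 therapists of six children per arm, analysed without a therapist term, rejected in 6.1% at ICC 0.02, 7.7% to 7.8% at 0.05, and 10.6% to 11.6% at 0.10 across repeated runs. With only MATCH clustered, the results were about 6.1% to 6.9% at 0.05 and 7.8% to 8.3% at 0.10. In 20,000 null trials at each ICC, a test on therapist means stayed at 5.0% to 5.3%.

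**Power of a valid analysis at N = 280, both arms clustered.** Effective N = 280 / DE.

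- ICC 0.05: 280 / 1.25 = 224; power 0.73 one-sided or 0.61 two-sided. Keeping 80% power needs 276 × 1.25 = 345 one-sided or 350 × 1.25 = 438 two-sided.
- ICC 0.10: 280 / 1.50 = 187; power 0.66 one-sided or 0.54 two-sided.

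**The case against.** The strongest objection is that this is silence rather than error. A journal article condenses the protocol, the analysis plan is not shown, and random-effects structure is often settled there. The article never says outright that children are treated as independent. It remains possible that a later document adds a therapist term. But the article does not leave the model open: it names the model class and the kinds of covariate, and keeps mixed-effects models for trajectories. A plan with a therapist random effect would replace the stated main-effects model, not complete it.

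Three stronger readings are tempting, and the article does not support them.

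- A reader might infer that the 5% level is broken by a known amount. The ICC is not given. At zero there is no inflation, and at 0.01 to 0.02 it is small.
- A reader might infer that every therapist treats about six children. The article expects at least six, and only for MATCH therapists; for TAU it matches the number of cases, not the load per therapist. Lighter TAU loads soften the problem without removing it.
- A reader might infer that only the analysis wording needs to change. Valid power is lower than stated, so the sample-size statement is affected too.

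Site also matters. If arms are balanced within site, leaving site out makes the test somewhat conservative and offsets part of the inflation. With site and therapist ICCs both assumed at 0.05, the factor is about 1 − 0.05 + 5 × 0.05 = 1.20, giving about 7.4% instead of 8.0%. The offset is partial and depends on that balance.

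**Conclusion.** The point holds as a conditional statement. The stated main-effects model omits therapists who are nested in arm, and for any positive therapist ICC its standard error is too small. The direction follows from the design; the size does not, because it rests on an assumed ICC of 0.01 to 0.10, six cases per therapist, and an unknown TAU load.

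On those assumptions a nominal 5% two-sided test runs at about 5.6% to 11% with both arms clustered, or about 5.3% to 8% with only MATCH clustered. In the former case the true standard error is about 2% to 22% larger than reported. The affected comparisons are primary outcomes, so the model should be settled before outcome data are analysed.

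**What to change.** Under For main effects, replace the general linear model with a linear mixed model that has a therapist random intercept and small-sample degrees of freedom, for example Kenward-Roger. Let the therapist variance differ by arm where it can be estimated. Where TAU therapists have single cases, it cannot be separated from residual variance and the term should be dropped for them. Cluster-robust standard errors with a small-sample correction are an acceptable alternative.

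Add a site term, because randomisation is within site. Carry the therapist term into the trajectory models, and report the therapist ICC by arm.

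Clinics already report each family's therapist after randomisation, so no new data are needed. The cost is wider confidence intervals and a sample-size statement that must be restated with a design effect, an ICC range and the sidedness of the test. At ICC 0.05 with both arms clustered, the restated power for 280 children is about 0.73 one-sided or 0.61 two-sided. Clustering takes this power in any case; the present model only hides the loss.
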